### Statistical analysis

The representativeness of the sample will be assessed by comparing observed proportions to expected proportions derived from Australian Bureau of Statistics population data using χ^2^ goodness-of-fit tests. The RE-AIM quantitative components will be described as counts and percentages with 95% CIs, and qualitative components will be thematically analysed (see table 2). Associations between participant demographic characteristics and quit rates will also be estimated using logistic regression models, as secondary exploratory analyses. Causal machine learning models^31^ will be used to assess potential heterogeneity in effectiveness of implementation strategies by participant subgroups. An ITT analysis will be performed for all effectiveness cessation outcomes, where participants with missing smoking or vaping cessation outcomes are classified as smokers or vapers. Multiple imputation using chained equations will be used to classify all remaining missing outcomes, as well as missing data on confounders. Attrition will be reported in the participant flow chart, and the baseline demographic and smoking/vaping characteristics of completers and non-completers will be compared via t-tests and χ^2^ tests as appropriate. Complete case results will also be reported to provide transparency and allow comparison across analytical methods.^42^ The proportion of participants with a quit attempt longer than 24 hours will be estimated within the subgroup of participants who have not been continuously abstinent at the 3, 6 and 12-month follow-ups.

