**Methods and analysis:**

A national single-group hybrid type 2 effectiveness-implementation study with 2000 Aboriginal and/or Torres Strait Islander people who use cigarettes and/or e-cigarettes (vapes) daily, want to quit and are aged ≥18 years. Participants will receive access to a culturally tailored mailed quit pack that includes up to a 12-week supply of nicotine replacement therapy, phone-based behavioural counselling and access to an online support forum. Cessation outcomes including 7-day point prevalence abstinence, prolonged abstinence and quit rates will be evaluated at 3, 6 and 12 months. An intention-to-treat approach will be used for cessation outcomes, with participants lost to follow-up classified as smokers or vapers. Exploratory logistic regression analyses will examine factors associated with quitting, and causal machine learning methods will be used to explore variation in intervention effectiveness across participant subgroups. The Reach-Effectiveness-Adoption-Implementation-Maintenance framework will guide evaluation of implementation and effectiveness outcomes. Analysis measures include cessation and quit attempt rates, number of participants recruited, representativeness and intervention uptake. The Consolidated Health Economic Evaluation Reporting Standards (CHEERS) will guide the cost-effectiveness analysis.

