### Study design and implementation framework

This study will use a pragmatic hybrid type 2 effectiveness-implementation design^32^ to examine the impact of the *Which Way? Quit Pack* intervention on individual cessation outcomes, while also gathering data to evaluate the implementation and inform sustainable national implementation. This design was chosen in recognition of the challenges of implementing high-quality controlled trials in Indigenous context broadly,^33^ and specifically in Indigenous smoking cessation studies,^34^ and to provide all participants who want to quit with immediate support. Evaluation of study implementation outcomes will be guided by the RE-AIM framework^28^ to assess programme outcomes comprehensively to inform and enhance real-world integration.

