	Participant representativeness including age, gender, geographical location, remoteness classification (using the Socio-Economic Indexes for Areas (SEIFA)) and current access and use of Aboriginal health services.	Participant survey Quantitative analysis	Baseline
**Effectiveness** Determine the impact of the *Which Way? Quit Pack* intervention on smoking and vaping cessation rates at 3, 6 and 12-month follow-ups, with a primary focus on abstinence at 12 months.	Self-reported 7-day prevalence abstinence.	Participant survey Quantitative analysis	3, 6 and 12 months post-baseline
	Prolonged abstinence.	Participant survey Quantitative analysis	3, 6 and 12 months post-baseline
	Number of quit attempts lasting ≥24 hours.	Participant survey Quantitative analysis	3, 6 and 12 months post-baseline
	Biochemical verification of smoking status.	Carbon monoxide via Smokerlyzer Quantitative analysis	3, 6 and 12 months post-baseline
**Adoption** Determine the extent to which participants use each component of the *Which Way? Quit Pack* intervention*.*	Absolute number and proportion of participants who complete each survey.	Participant survey Quantitative analysis	Baseline and 3, 6 and 12 months post-baseline
	Representativeness (age, gender, geographical location, remoteness classification (using SEIFA)) of participants who complete each survey.	Participant survey Quantitative analysis	Baseline and 3, 6 and 12 months post-baseline
	Uptake and frequency of use of intervention components including nicotine replacement therapy (NRT), phone-based behavioural counselling and participation in the online forum.	Data from trial tracking systems (NRT pack requests, behavioural support records and online forum use) Quantitative analysis	Baseline to end of intervention (3-month follow-up)

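### With everyone offered the pack, causal machine learning cannot show in whom the pack works better; it can show who is abstinent, and missing-as-smoker mixes that with who answers surveys

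*Protocol article*

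**What the plan says.** The abstract describes "A national single-group hybrid type 2 effectiveness-implementation study with 2000 Aboriginal and/or Torres Strait Islander people". The section on study design and implementation framework explains that the design was chosen partly "to provide all participants who want to quit with immediate support". There is no comparison arm.

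The two descriptions of the subgroup work differ:

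- Abstract, methods and analysis: "causal machine learning methods will be used to explore variation in intervention effectiveness across participant subgroups".
- Statistical analysis: causal machine learning models "will be used to assess potential heterogeneity in effectiveness of implementation strategies by participant subgroups".

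Beside these stands a conventional model: "Associations between participant demographic characteristics and quit rates will also be estimated using logistic regression models, as secondary exploratory analyses".

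For missing data, the Statistical analysis section applies an intention-to-treat rule to all cessation outcomes, "where participants with missing smoking or vaping cessation outcomes are classified as smokers or vapers". Chained-equation imputation is kept for the other missing outcomes and for confounders. The section adds: "Complete case results will also be reported to provide transparency and allow comparison across analytical methods". It also plans a baseline comparison of completers with non-completers.

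The strengths and limitations box and the Discussion both concede that a single group restricts causal conclusions. The Discussion says that cessation rates will be read as estimates of what happens in practice.

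**The concern.** An effect of the pack is the quit rate with it minus the quit rate without it. Here the second term is not observed for anyone. A model that relates subgroup to quitting therefore returns differences in quit rates, whatever the algorithm, and those mix prognosis with effect. The abstract nevertheless gives the effect itself as the target. That goes further than the document's own limitations, and it is a different target from the one in the Statistical analysis section.

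The missing-outcome rule adds a second difficulty. It is a familiar conservative choice for one overall rate. In a comparison of subgroups it multiplies each subgroup's responder quit rate by its follow-up rate, so a subgroup that answers fewer surveys appears to quit less.

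The study is meant to inform national implementation. If the output is read as showing where the pack works best, communities that merely respond less often could be judged to benefit less.

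**Working it through.** The plan gives no figure for the subgroup models, so there is nothing of its own to reproduce on this point. The check has three parts.

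**1. Can a difference in effect be identified?** Effect in a subgroup = observed quit rate − untreated quit rate. Take illustrative observed rates of 25% in subgroup A and 15% in subgroup B:

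| Assumed untreated rate, A / B | Effect, A / B | Difference in effect (points) |
|---|---|---|
| 5% / 5% | 20 / 10 | +10 |
| 15% / 5% | 10 / 10 | 0 |
| 20% / 5% | 5 / 10 | −5 |
| 5% / 15% | 20 / 0 | +20 |

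All four rows fit the same trial data. The study observes no untreated rate, so it cannot choose among them.

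**2. Which contrasts exist within the study?**

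- Fixed at or before baseline: recruitment route (Participant recruitment), and the NRT option and dose pack (Table 1 and the section on the mailed pack). The dose pack follows from baseline smoking and vaping, so its contrast is tied to that behaviour.
- Taken up after baseline: opt-in counselling, forum use, and the second NRT shipment, which is sent on confirmation at 6 weeks. Table 2 records uptake over a window that closes at the 3-month assessment. Early quitting or relapse can change uptake within that window.

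Comparisons of participants who differ in these components are possible, but they are observational.

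**3. What does missing-as-smoker do to subgroup comparisons?** Inputs from the Introduction: pilot N = 165, with 6-month abstinence of 34% (complete case) and 19.4% (intention to treat).

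- Quitters: 0.194 × 165 = 32.
- Respondents: 32 / 0.34 = 94.
- Implied follow-up: 94 / 165 = 57%, so about 43% were set to smoker.

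Subgroup rate under the rule = responder quit rate × follow-up. Responder quitting is held at 34% in both subgroups, with 1000 in each. Follow-up is varied around 57%; these splits are assumptions.

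| Follow-up | Rate under the rule | Odds ratio | Chance of p < 0.05 (two-sided) |
|---|---|---|---|
| 57% vs 57% | 19.4% vs 19.4% | 1.00 | 4.9% (simulated) |
| 62% vs 52% | 21.1% vs 17.7% | 1.24 | about 49% |
| 67% vs 47% | 22.8% vs 16.0% | 1.55 | about 97% |

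For the last row: 0.34 × 0.67 = 0.228 and 0.34 × 0.47 = 0.160, so the odds ratio is (0.228/0.772) / (0.160/0.840) = 1.55. The complete-case difference is zero in every row.

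How much of the difference is artefact depends on quitting among non-responders. If that rate is q in both subgroups, the spurious part is q × follow-up gap. With a 20-point gap it runs from 0 (q = 0, where the rule is exactly right) to 0.34 × 20 = 6.8 points (q = 34%, where the whole difference is artefact).

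**The case against.** The best defence starts from the Statistical analysis section. It speaks of implementation strategies, not of pack versus no pack, and it mentions confounders. Both fit an observational contrast among participants, and several components do have non-users. This stands: a reader might infer that causal models can estimate nothing here, and the document does not support that. Nor does it support the inference that the only exposures are ones altered by early quitting, because the NRT option, the dose pack and the recruitment route are settled at or before baseline. The defence does not rescue the abstract, which names the effectiveness of the intervention itself.

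It is also fair that exposures, landmarks and adjustment sets normally belong in an analysis plan. Their absence from an article is not held against it. The point concerns the target as written.

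The analysis is presented as exploration of potential heterogeneity, and the logistic models are correctly labelled as associations. Only the missing-data point applies to them.

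On missing data, complete-case results and the completer comparison are planned and would help to show an artefact. The article does not say that the subgroup models will use only the missing-as-smoker version, and it does not tie the complete-case results to those models. Complete-case estimates are unbiased only if drop-out is unrelated to quitting within subgroup. The follow-up gaps above are assumed, and the 57% comes from one pilot of 165 people. The Sample size section quotes 16% for the pilot at 6 months; against 34% that would imply 0.16 / 0.34 = 47% follow-up.

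**Conclusion.** The concern holds for the stated target. Variation in the effectiveness of the pack across subgroups cannot be identified in a single group where all are offered it, and the abstract's wording conflicts with both the analysis section and the conceded limitations. This rests on the design alone and needs no numerical assumption. Subgroup differences in abstinence can be described. Component contrasts can be estimated only under strong no-confounding assumptions, with an added problem of reverse causation for components taken up after baseline.

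The missing-as-smoker limb is a demonstrated risk that the plan partly covers. An odds ratio of 1.24 to 1.55 follows from an assumed follow-up gap of 10 to 20 points around 57%, equal responder quitting of 34% and 1000 per subgroup. It is wholly spurious only if non-responders quit as often as responders. A reader might infer that the subgroup results will be biased by this amount; the document gives no follow-up by subgroup, so it does not support that. The primary 12-month rate is not affected by this point.

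**What to change.** - Align the abstract and the Statistical analysis section. Restate the aim as exploratory prediction of 12-month abstinence by baseline characteristics, and drop the phrase about variation in intervention effectiveness.
- If component contrasts are kept, use exposures fixed at baseline, or uptake by a landmark that precedes the outcome, and label the results associational.
- Report the machine-learning and logistic models on multiply imputed and complete-case cessation outcomes alongside missing-as-smoker. Keep missing-as-smoker for the headline rate.

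The cost is a change of wording and one more imputation model; chained equations are already planned for other variables. Imputation brings a missing-at-random assumption that cannot be tested, which is why the three versions should stand side by side. The claims become more modest.

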### Cost-effectiveness analysis

The cost-effectiveness analysis (CEA) will follow the Consolidated Health Economic Evaluation Reporting Standards (CHEERS 2022), assessing both costs and health outcomes associated with national delivery of the *Which Way? Quit Pack*. A trial-based CEA will be conducted from the health system perspective, capturing all intervention delivery costs (NRT supply, postage, staffing, behavioural counselling, digital infrastructure and administrative overheads) and participant healthcare utilisation. Resource use will be tracked prospectively using project financial records and participant-reported healthcare contacts, with unit costs sourced from standard Australian cost schedules. Health-related quality of life will be measured using the SF-8D, enabling estimation of quality-adjusted life years (QALYs). Incremental cost-effectiveness ratios will compare intervention costs with QALYs gained and with validated cessation outcomes. Sensitivity analyses will test assumptions around missing data, NRT uptake and cost variation.

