**Implementation** Determine the fidelity, quality and consistency of the *Which Way? Quit Pack* intervention delivery, as well as the barriers and facilitators encountered during the implementation process*.*	Qualitative process evaluation using staff feedback to assess fidelity, barriers and facilitators to delivery. Evaluation will be guided by three questions: (1) ‘what worked well?’ to identify effective strategies, resources or processes supporting implementation; (2) ‘what has not worked well?’ to explore challenges, barriers or gaps experienced; and (3) ‘what changes need to be made?’ to gather suggestions for addressing barriers and improving implementation.	Implementation review meetings with project staff Qualitative analysis	Weekly
**Maintenance** Determine the long-term sustainability of the *Quit Pack* intervention on smoking and vaping cessation at 12-month follow-up and conduct a health economic evaluation to inform scalability and sustainability of the intervention for continued use and support within the community and healthcare settings beyond the study period.	Self-reported 7-day point prevalence abstinence at 12-month follow-up.	Participant survey Quantitative analysis	12 months post-baseline
	Prolonged abstinence at 12-month follow-up.	Participant survey Quantitative analysis	3, 6 and 12 months post-baseline
	Optional biochemical verification of smoking status at 12-month follow-up.	Participant survey Quantitative analysis	12 months post-baseline
	Cost-effectiveness of the intervention including cost per participant, health-adjusted life years gained, hospitalisations averted and number of quitters.	Participant surveys using Short-Form 8 Health Survey (SF-8D) Quantitative analysis	Baseline and 3, 6 and 12 months post-baseline

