This study has a number of strengths, including its pragmatic, real-world design, anticipated recruitment of a large national sample and the use of a comprehensive evaluation framework that includes examination of both effectiveness and implementation outcomes. To our knowledge, *Quit Pack* is the first national Aboriginal and Torres Strait Islander smoking and vaping cessation intervention to embed Indigenous leadership and governance throughout all aspects of intervention development, design and delivery, reflecting a culturally grounded and self-determined approach. However, some limitations should be noted. The single-group design without a comparison arm limits the ability to attribute observed effects solely to the intervention. As such, cessation rates will be interpreted as estimates of real-world outcomes. Reliance on self-reported cessation outcomes may introduce recall and social desirability bias and influence estimated abstinence rates, although this is partially mitigated through optional biochemical verification, which will also provide critical feasibility data for implementation into future studies. Finally, while the study is designed to maximise reach and feasibility of delivering cessation support to a large and diverse group of Aboriginal and Torres Strait Islander people, the pragmatic considerations for a trial of this nature necessarily limit the degree of experimental control, including obtaining detailed data about intervention fidelity, adherence and the relative contribution of individual intervention components, which may impact the generalisability of findings.

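### The planned incremental cost-effectiveness ratios have no comparator: the study has one group, none is named, and the listed sensitivity analyses do not vary one

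*Protocol article*

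**What the plan says.** The Cost-effectiveness analysis section sets the type of evaluation: "A trial-based CEA will be conducted from the health system perspective". It lists the delivery costs and participant healthcare use to be captured, and bases QALYs on the SF-8D. It then sets the ratios: "Incremental cost-effectiveness ratios will compare intervention costs with QALYs gained and with validated cessation outcomes". On robustness it says: "Sensitivity analyses will test assumptions around missing data, NRT uptake and cost variation".

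Table 2, under Maintenance, gives the cost-effectiveness outcomes as "cost per participant, health-adjusted life years gained, hospitalisations averted and number of quitters". The data source shown for that row is the SF-8D participant survey.

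The design is single-group throughout (Abstract, Study aims, Strengths and limitations). The Discussion acknowledges what follows from that: "The single-group design without a comparison arm limits the ability to attribute observed effects solely to the intervention". Its next sentence settles how one kind of result is to be read: "As such, cessation rates will be interpreted as estimates of real-world outcomes". It says nothing equivalent about the economic ratios.

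**The concern.** An incremental ratio is a difference in cost divided by a difference in effect between two courses of action. The article names only one. The numerator it gives is the cost of the intervention rather than a cost difference, and the trial will hold no data on people who did not receive the pack. Gains in life years and averted hospitalisations likewise mean something only against what would have happened otherwise, and a quality-of-life questionnaire given to one group cannot supply that.

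Eligibility requires that participants want to quit, and the Introduction describes other cessation supports, so some quitting without the pack is plausible. If it is not subtracted, the figure reported as cost per additional quit is really cost per quit observed. Cost-effectiveness is one of the stated aims and is meant to inform national implementation, so the label affects what a funder would conclude.

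**Working it through.** The article states no ratio, cost, utility or background quit rate, so there is no figure of the plan's own to reproduce. The size can only be illustrated.

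**Inputs**
- N = 2000 (Sample size).
- p = 16%: pilot 7-day point prevalence at 6 months (Sample size).
- p = 19.4%: pilot 6-month 7-day abstinence by intention to treat (Introduction). The article gives both pilot figures, so both are used.
- p = 5%: the assumed 12-month minimum (Sample size).
- b, the quit rate without the pack: not in the document. Assumed 3%, 5% and 8%.

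Both pilot rates are self-reported at 6 months. Neither is the 12-month or the validated outcome.

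**Cost per quit.** Let C be the intervention cost per participant, and treat the alternative as costing nothing extra.
- Without a comparator: C / p.
- Incremental: C / (p − b).
- Factor by which the first understates the second: p / (p − b).

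| p | b | Factor | Quits in 2000, gross | Net of background |
|---|---|---|---|---|
| 16% | 3% | 0.16/0.13 = 1.23 | 320 | 260 |
| 16% | 5% | 0.16/0.11 = 1.45 | 320 | 220 |
| 16% | 8% | 0.16/0.08 = 2.00 | 320 | 160 |
| 19.4% | 3% | 0.194/0.164 = 1.18 | 388 | 328 |
| 19.4% | 5% | 0.194/0.144 = 1.35 | 388 | 288 |
| 19.4% | 8% | 0.194/0.114 = 1.70 | 388 | 228 |

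At the 5% planning minimum with b = 3%, the factor is 0.05/0.02 = 2.5, and 100 gross quits become 40 net. That is a near-worst case, not an expectation, because 5% is a floor.

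**Cost per QALY.** Suppose utility changes linearly by d over one year in participants, and would have changed by c without the pack. The before-after gain is d/2 and the net gain is (d − c)/2. Take d = +0.01 (assumed).
- If c = +0.005: before-after 0.005, net 0.0025. The uncontrolled ratio is twice too favourable.
- If c = −0.01: before-after 0.005, net 0.010. The uncontrolled ratio is twice too unfavourable.

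The sign of the error depends on a trend that the study cannot observe.

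**Outcome lists.** The economic section names QALYs and validated cessation. Table 2 names health-adjusted life years, averted hospitalisations and number of quitters. The two lists do not match.

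**The case against.** The strongest reply is that a journal article condenses its economic plan, and that an external or modelled comparator may sit in a fuller document. Table 2 even hints at modelling, since a 12-month SF-8D survey cannot itself yield averted hospitalisations. This has force against any claim about what the analysts will actually do. It does not dispose of the point, because the article does more than stay silent: it calls the analysis trial-based, gives the numerator and denominators, and lists sensitivity analyses in which the counterfactual does not appear.

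A second reply is that the limitation is disclosed. It is, and the Discussion's wording about observed effects is not confined to cessation. But the stated consequence covers cessation rates only, while the economic section still promises a ratio that requires attribution.

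Three stronger readings are tempting, and the document does not support them.
- *A reader might infer that every quit and every QALY change will be credited to the pack.* No section says so. It would follow only from an implicit comparator of zero or of baseline.
- *A reader might infer that all the ratios will come out too favourable.* This holds for cost per quit only, other things equal. Optional CO verification and counting missing outcomes as smoking or vaping can both push counted quits below true quits. Including healthcare use that would have occurred anyway would raise the numerator. For QALYs the direction is open.
- *A reader might infer that the missing counterfactual matters more than any other assumption.* The pilot's 6-month rate was 34% in complete cases and 19.4% by intention to treat, so missing-data handling alone moves it by 34/19.4 = 1.75. That exceeds most of the factors tabulated at the pilot rates, and the plan already lists missing data as a sensitivity analysis.

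**Conclusion.** The point holds in a limited form. The article commits to incremental ratios within a trial-based analysis of a single group, names no comparator, and does not test the counterfactual. Followed as written, the cost-per-quit figure is an average ratio under an incremental label. Other things equal, it understates the cost per additional quit by about 1.2 to 2.0 times at the pilot rates. That range rests on assumed background rates of 3% to 8%, on 6-month self-reported abstinence standing in for a 12-month validated outcome, and on cost held fixed. The cost per QALY cannot be interpreted as incremental, and its bias has no known sign.

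This should be fixed. It changes what the cost-effectiveness aim can conclude, but it does not touch enrolment or the primary abstinence analysis.

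**What to change.** Choose one of two routes.

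(a) Report cost per participant and average cost per quitter under those names, and remove the terms incremental, gained and averted from the economic section and Table 2.

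(b) Keep the incremental ratios, but name the comparator (no Quit Pack, or usual care). Take its 12-month quit rate, cost and utility from a cited source, and label the result as modelled. Add the background quit rate to the sensitivity analyses, with the threshold value at which the conclusion would change.

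Under either route, make the Table 2 outcomes agree with the economic section: QALYs or health-adjusted life years, and averted hospitalisations only if a source for them is given.

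The cost is redrafting under (a), and slightly more analysis work under (b), where cost per quit will also look less favourable. Neither route needs a control arm or more participants.
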